### Data collection and transfer

An anonymisation tool will be applied to all images and datasets will be coded with participants’ unique Study ID before transfer. Image data will be uploaded to a data-sharing platform created and maintained by the University of Sydney for this study via a site-specific unique link to study folders. To quantity the interobserver error, the image data will be independently manually delineated by a separate study site.

All other data will be obtained from the participant’s medical record by delegated study personnel at the recruiting site and entered in a password-protected online database (REDCap 12.5.8, Vanderbilt University), coded by Study ID and year of birth.

### Bias

The study design minimises bias/errors due to sampling (baseline characteristics), matching (accuracy of comparator delineation) and assessments. Baseline characteristics to be considered in final analyses include (i) type, size, shape, density, and location of the contrast agent, (ii) type of imaging and treatment machine, (iii) time since TACE, (iv) participant demographics, and (v) treatment site. Accuracy of the ground truth (manual contrast mass delineation on images) will be maximised by (i) providing sites with the same purpose-designed software to conduct delineation of contrast mass location on images, (ii) for the same projections, performing ground truth delineation by an independent observer who is a member of the research team from another site, and (iii) assessment by qualified and experienced medical physicists or radiation therapists. Final assessment of the KIM software (comparator) will be conducted (i) on images that have not been marked with the ground truth, (ii) by site study personnel who have not seen images marked with ground truth, (iii) by study personnel who are qualified and experienced medical physicists.

### Outcome measures

(i) the proportion of CBCT projection and intra-treatment images in which the KIM software detects a contrast mass. (ii) the mean and standard deviation of the difference (mm) of location of the centre of the contrast mass detected on CBCT projection and intra-fraction images by KIM software compared with the ground truth in each of the horizontal and vertical directions. (iii) the mean and standard deviation of the centroid error between the segmentation and ground truth will be calculated, and DICE analysis will be performed to measure the similarity between the two delineation methods. Characteristics of the participants, chemotherapy, RT, and images, (e.g., treatment machine type, treatment site; contrast agent type, density, size, shape, and location; and patient size, age, cancer stage and sex), will be used to create a generalised linear model, or appropriate alternative, to identity univariate and multivariate patient or treatment features that contributed to the success or failure of the KIM tracking algorithm.

### Preliminary data

To investigate the feasibility of the ROCK-RT protocol, data from three patients recruited into ROCK-RT have been analysed. A conditional generative adversarial network [18] was used to train a patient-specific model to track the contrast mass from the pre-treatment data including data augmentation (translation and rotation). This model was then applied to the data acquired during treatment, representing the clinical scenario of real-time target tracking. Figure 4 shows examples of the target tracking prediction compared with the ground truth. Figure 5 quantifies the centroid error and Dice similarity coefficient acquired from two fractions for three patients using 35 images per fraction. The mean and standard deviation of the centroid tracking error in the anterior-posterior/lateral and super-inferior directions were − 0.4 ± 2.8 mm and − 0.6 ± 1.4 mm respectively. The mean Dice similarity coefficient was 0.87 ± 0.08.

**Fig. 4 Fig4:**
[figure not shown]
Examples of the target tracking prediction compared with the ground truth on kV images from different imaging angles from one fraction of one patient

**Fig. 5 Fig5:**
[figure not shown]
The centroid error and Dice similarity coefficient acquired from two fractions for three patients. AP = Anterior-Posterior; LAT = Lateral; SI = Superior-Inferior; DSC = Dice similarity coefficient

## Discussion

The detection of residual radio-opaque contrast in the liver by KIM may lead to the development of technology that improves the accuracy, safety, and effectiveness of RT for liver cancer. The main challenges to this study are the availability of participants whose minimum image dataset is available, especially for retrospectively recruited participants, and the time commitment required by sites to contour images.

The hypotheses will be accepted if, in two thirds of participants (i), KIM detects the contrast mass; (ii) the mean and standard deviation (mm) difference in the location of the mass between ground truth and KIM detection are ≤ 2 mm and ≤ 3 mm, respectively and (iii) if a model of the success rate in the primary hypothesis and patient/treatment characteristics can predict KIM success in 85% of participants. Should the three hypotheses be accepted, there will be sufficient justification for the prospective use of KIM as a real-time image guided radiation therapy tool for liver cancer patients.

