### Hypotheses

We hypothesise that: (i) deep learning software can be developed that will successfully track the contrast agent mass on two thirds of cone beam computed tomography (CBCT) projection and intra-treatment images (ii), the mean and standard deviation (mm) difference in the location of the mass between ground truth and deep learning detection are ≤ 2 mm and ≤ 3 mm respectively and (iii) statistical modelling of study data will predict tracking success in 85% of trial participants.

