### Datasets

The minimum RT treatment dataset required from retrospectively recruited participants includes the 3D or 4D CT scans used for planning, contours, treatment plans and pre-treatment 3D or 4D CBCT reconstructed images in DICOM format, and 2D projection images. In-treatment x-ray images are mandatory for prospectively recruited participants and desirable from those retrospectively recruited and any additional images from screening or testing sessions are desirable but not mandatory from all participants.

In addition to RT treatment images, data will be collected on participant characteristics (demographics, medical history, diagnosis), TACE chemotherapy (type of contrast agent - ethiodised oil or drug eluting beads, date of procedure), and other RT treatment-related data (treatment centre and treating doctor, treatment device and version, imaging system type/model, motion management techniques such as free-breathing or breath hold, the use of abdominal compression, and breathing training).

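### The fixed accuracy limits (mean ≤ 2 mm, SD ≤ 3 mm) ignore how far the mass moved, so in low-motion participants a pass does not show tracking

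*Protocol article*

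**What the plan says.** The Hypotheses section sets the accuracy target as a "difference in the location of the mass between ground truth and deep learning detection are ≤ 2 mm and ≤ 3 mm respectively". The Discussion turns it into a rule counted over participants: "The hypotheses will be accepted if, in two thirds of participants (i), KIM detects the contrast mass", and, for hypothesis (ii) on accuracy, "the mean and standard deviation (mm) difference in the location of the mass between ground truth and KIM detection are ≤ 2 mm and ≤" (the second limit being 3 mm). It then treats acceptance of all three hypotheses as enough to justify using KIM prospectively for real-time guidance.

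Outcome measures defines the error as "the mean and standard deviation of the difference (mm) of location of the centre of the contrast mass detected" by KIM against ground truth, "in each of the horizontal and vertical directions". The detection outcome is "the proportion of CBCT projection and intra-treatment images in which the KIM software detects a contrast mass", with no requirement on position. Dice is calculated, but it has no threshold and is not part of the acceptance rule. The only comparison named is KIM against manual delineation.

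Among the data items, the Datasets section lists "motion management techniques such as free-breathing or breath hold, the use of abdominal compression, and breathing training". Eligibility criteria excludes none of these techniques and sets no minimum motion. The Background calls liver tumour motion significant but gives no amplitude in millimetres.

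Preliminary data reports centroid errors for three patients that "were − 0.4 ± 2.8 mm and − 0.6 ± 1.4 mm respectively" (anterior-posterior/lateral, then superior-inferior), without the spread of the motion in the same images.

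**The concern.** The Aim section asks whether retained contrast can be used to follow tumour motion in real time. A limit on KIM minus ground truth answers that only if software that follows nothing would fail it. If the mass hardly moves, an output stuck at one position is also close to the truth, and the participant counts as a success either way.

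Nothing else in the rule closes the gap. Detection requires only that a mass is found, and Dice plays no part in acceptance. Hypothesis (iii) models success as these rules define it, so it carries the ambiguity forward. What is at stake is the last step of the Discussion, from meeting the limits to a justification for real-time tracking. The pass rate would also depend partly on the mix of motion management among those recruited.

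**Working it through.** The article gives no derivation for the 2 mm and 3 mm limits, so there is no figure of the plan's own to reproduce. The check asks how much motion a fixed output could leave untracked and still pass.

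**Inputs from the article.** Mean ≤ 2 mm and SD ≤ 3 mm (Hypotheses, Discussion); two thirds of 50 participants, that is 33.3, so 34 (Discussion, Eligibility criteria); 35 projections per CBCT per fraction (Matching); pilot errors −0.4 ± 2.8 mm and −0.6 ± 1.4 mm (Preliminary data), which show that the mean is signed.

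**Assumptions.** Peak-to-peak motion A from 3 to 20 mm; sinusoidal, cos^4 or cos^6 traces; matching noise of 0, 1.4 or 2.0 mm SD; limits applied per participant, as the Discussion words it.

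**1. Fixed at the mean position, sinusoidal motion.** Mean error is 0 and error SD = A/(2√2) = 0.354A. Setting this to 3 mm gives A = 3 × 2√2 = 8.49 mm.

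| A (mm) | error SD (mm) | SD ≤ 3 mm? |
|---|---|---|
| 3 | 1.06 | yes |
| 5 | 1.77 | yes |
| 8 | 2.83 | yes |
| 10 | 3.54 | no |
| 15 | 5.30 | no |
| 20 | 7.07 | no |

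**2. Trace shape.** For cos^4 the SD is 0.364A, giving 3/0.364 = 8.2 mm. For cos^6 it is 0.358A, giving 8.4 mm.

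**3. Matching noise of SD e.** The largest passing A is √(9 − e²)/0.354 for the sinusoid.
- e = 1.4: √7.04 = 2.65, giving 7.5 mm (7.3 for cos^4, 7.4 for cos^6).
- e = 2.0: √5 = 2.24, giving 6.3 mm (6.1 and 6.3).

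Random between-fraction shifts act in the same way: an SD of 1 mm gives 8.0 mm and 2 mm gives 6.3 mm.

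**4. Fixed at end-exhale.** The mean error is now 0.5A (sinusoid), 0.375A (cos^4) or 0.3125A (cos^6). The 2 mm mean limit binds first: 2/0.5 = 4.0 mm, 2/0.375 = 5.3 mm and 2/0.3125 = 6.4 mm.

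**5. Horizontal image axis.** For sinusoidal motion along one transverse axis, seen over a full gantry rotation, the SD is A/4. A fixed output at the mean position then passes up to 3 × 4 = 12 mm.

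**6. Finite images.** Simulation of case 1 without noise gives the chance that a fixed output meets both limits.

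| A (mm) | 35 images | 105 images (3 × 35) |
|---|---|---|
| 6 | 100% | 100% |
| 8 | 84% | 96% |
| 9 | 18% | 5% |
| 10 | 1% | 0% |

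**7. What a per-participant superiority rule would do.** Root-mean-square error is √(mean² + SD²). The pilot figures give √(0.16 + 7.84) = 2.83 mm and √(0.36 + 1.96) = 1.52 mm. A mean-centred static reference under sinusoidal motion has the same error at 2.83 × 2√2 = 8.0 mm and 1.52 × 2√2 = 4.3 mm. Below those amplitudes, KIM with pilot-like errors would lose to it while meeting both limits.

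**The case against.** The strongest reply is that this is a feasibility study of localisation. KIM's position is compared with manual delineation, and an absolute limit in millimetres is a normal way to judge that. If a mass moved little and KIM placed it within the limits, KIM located it correctly. That stands. It is a reason to keep the limits, and not to require each participant to beat a static reference (step 7).

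The software is also not a constant predictor: a patient-specific network segments each image. That is true, but the acceptance rule should be able to show it, and at low motion it cannot.

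The 8.5 mm figure is close to a best case for a fixed output on the vertical axis. Matching noise, between-fraction shifts or an offset reference bring it down to between 4.0 and 8.0 mm. It should be read with that range, and with the 12 mm transverse case in the other direction.

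Motion management is collected, and the model's covariate list in Outcome measures is given only as examples, so it could be included. That would describe who succeeds, but would not change what counts as success.

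Two stronger readings are tempting. A reader might infer that the whole study could pass without tracking. The article does not support this: a mean-centred fixed output fails on the vertical axis once motion exceeds about 8.5 mm, two thirds of participants must pass, and neither amplitudes nor numbers treated in breath hold or with compression are given. A reader might also infer that the pilot did not track, since SDs of 1.4 and 2.8 mm are what a fixed output would give at 4.0 and 7.9 mm. That coincidence is no evidence of it. The figures come from three patients, and the mean Dice coefficient was 0.87. Without the motion SD, the reported centroid errors alone do not settle the question either way.

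**Conclusion.** The point holds for participants with small or controlled motion. For them the limits show that the mass was located, not that its movement was followed. Under the assumed traces, a fixed output at the mean position passes up to about 8.5 mm peak to peak without noise and about 6 to 7.5 mm with 1.4 to 2.0 mm of matching noise. Fixed at end-exhale, it passes up to about 4.0 to 6.4 mm. These figures rest on the breathing model, the noise assumption and the participant-level reading of the Discussion. The share of the 50 participants in that range cannot be worked out from the article. The limits are not wrong as accuracy criteria; the step from meeting them to a claim about real-time tracking is unsupported where motion is low.

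**What to change.** Keep 2 mm and 3 mm as the localisation-accuracy criterion, with every participant in the two-thirds denominator. In addition:

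- For each participant and direction, compute from the existing ground-truth positions the motion SD and the error of a static reference.
- Set that reference before the analysed images, for example the planning position or the pre-treatment matched position. Do not use the mean of the same acquisition: for CBCT projections, a position matched on that same CBCT is close to an after-the-fact mean and would favour the static reference.
- Report KIM error beside static-reference error, overall, by motion amplitude and by motion management technique. Give mean and SD separately, so that a constant offset in the reference is not credited to KIM as tracking.
- Amend the Discussion so that the justification for real-time tracking also rests on KIM's error being smaller than the static-reference error across participants, in particular those whose motion exceeds an amount fixed before results are seen. Describe low-motion passes as localisation accuracy only.

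The ground-truth positions and motion management data are already planned, so the work is a small addition to the analysis. The price is that the tracking conclusion may be less favourable than the headline pass rate.

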**Fig. 2 Fig2:**
[figure not shown]
Study Design. Standardly collected radiation therapy planning, CBCT projections and intra-treatment monitoring images will be used to created manually delineated matches. After improvement of existing mass-detecting software (KIM) through machine learning, the updated algorithm will be applied to un-delineated images to (i) detect the contrast mass, and (ii) locate its centre in comparison with manually delineated matches. If the contrast mass can be detected accurately, modelling for likelihood of KIM tracking success will be conducted

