### Eligibility criteria

This study will recruit 50 participants who: will be ≥ 18 years of age; had or will have SABR for HCC; will/have residual radio-opaque contrast (e.g., ethiodised oil or drug-eluting beads containing iodine) from prior TACE chemotherapy visible within the imaging field on RT planning CT scans; will provide written informed consent or meet criteria for a waiver of consent; and will have the minimum image dataset available in the required format.

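### The 85% prediction criterion for hypothesis (iii) ignores the observed success proportion and does not require out-of-sample accuracy, so it can be met without predictive value when tracking success is common

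*Protocol article*

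**What the plan says.** The Hypotheses section states that "statistical modelling of study data will predict tracking success in 85% of trial participants". The Discussion turns this into an acceptance rule: (iii) holds if "a model of the success rate in the primary hypothesis and patient/treatment characteristics can predict KIM success in 85% of participants". The same paragraph says that accepting all three hypotheses would justify prospective use of KIM in liver cancer patients.

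The sample size is in Eligibility criteria: "This study will recruit 50 participants who" meet the listed conditions. For hypothesis (i) the Discussion sets a participant-level mark: "The hypotheses will be accepted if, in two thirds of participants (i), KIM detects the contrast mass".

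Outcome measures describes the model. Participant, chemotherapy, radiotherapy and image characteristics "will be used to create a generalised linear model, or appropriate alternative", with the aim "to identity univariate and multivariate patient or treatment features that contributed to the success or failure of the KIM tracking algorithm". The characteristics given as examples are "treatment machine type, treatment site; contrast agent type, density, size, shape, and location; and patient size, age, cancer stage and sex". The caption of Fig. 2 places the modelling after detection: "If the contrast mass can be detected accurately, modelling for likelihood of KIM tracking success will be conducted".

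**The concern.** Classification accuracy depends on how common the outcome is. If most participants are tracked successfully, predicting success for all of them is accurate without using any characteristic. A fixed 85% mark with no reference to that baseline cannot separate an informative model from an empty one once success is frequent.

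The second weakness is that the rule does not say whether accuracy is measured on the participants used to fit the model or on participants held out. With 50 participants, few failures and a long list of candidate characteristics, the two can differ widely.

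The Discussion treats (iii) as one of three grounds for prospective use. If it is accepted in either of these ways, the article would report that tracking success can be predicted from patient and treatment features when the data had not shown it.

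**Working it through.** The article gives no derivation of the 85% mark or of the sample size, so there is no calculation of its own to reproduce.

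**Inputs.** N = 50 (Eligibility criteria); 85% (Hypotheses and Discussion); two thirds of participants for hypothesis (i) (Discussion); 11 characteristics named as examples (Outcome measures: two on treatment, five on contrast agent, four on the patient).

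**Assumptions.** Success is yes/no per participant, the 85% is accuracy over all 50, and the classification cut-off is 0.5.

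**Step 1: the mark as a count.** 0.85 × 50 = 42.5, so at least 43 correct. For hypothesis (i), 50 × 2/3 = 33.3, so at least 34 successes and at most 16 failures.

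**Step 2: the model with no predictors.** Predicting success for everyone has accuracy equal to the observed success proportion:
- 34/50 = 68%, fails
- 42/50 = 84%, fails
- 43/50 = 86%, passes

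The chance that it passes is P(X ≥ 43) with X ~ Binomial(50, p):

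| True success rate p | P(X ≥ 43) |
|---|---|
| 2/3 | 0.2% |
| 0.75 | 4.5% |
| 0.80 | 19% |
| 0.85 | 52% |
| 0.90 | 88% |
| 0.95 | 99.7% |

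Cross-validation does not alter this. With 43 successes and 7 failures, leaving out any one participant still leaves a majority of successes, so the held-out prediction is always success and the score is again 43/50.

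**Step 3: noise models scored in-sample.** Logistic regression was fitted to 50 participants with independent standard-normal predictors unrelated to outcome, 600 runs per cell. The entries are the proportion of runs with at least 43 correct on the fitting data:

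| Successes | 5 terms | 11 terms | 15 terms | 20 terms |
|---|---|---|---|---|
| 34 | 0% | 4% | 19% | 51% |
| 38 | 2% | 15% | 46% | 80% |
| 40 | 5% | 41% | 69% | 89% |
| 42 | 34% | 75% | 88% | 96% |

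Repeat simulations with 11 or 12 terms gave about 3–7% at 34 successes, 33–48% at 40 and 76–83% at 42. The 75% in the table agrees within simulation error: √(0.75 × 0.25 / 600) = 1.8 percentage points. More than 11 terms is possible, because coding multi-level factors (there are four recruiting sites) adds terms.

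**Step 4: the same noise models out-of-sample.** At 40 successes with 11 terms, mean accuracy is 84% in-sample and 71% on new data, below the 80% from predicting success for everyone. Under 10-fold cross-validation with 5 or 11 terms, noise models reached 43/50 in essentially no runs at 34 and 40 successes and in about 1–3% at 42.

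**The case against.** The strongest reply is that the article does not say the 85% is in-sample. It is a condensed account, and internal validation, penalisation and predictor selection are commonly left to a full protocol or analysis plan. The characteristics are examples, the model type is left open, and nothing says that 11 or more terms enter one unpenalised logistic model. This stands: Step 3 is conditional on a reading the text permits but does not state, and Step 4 shows that validation would almost remove the problem.

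It does not reach Step 2. The model without predictors scores the same with or without validation, and the 85% threshold is fixed in the article itself.

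A reader might infer that hypothesis (iii) tests nothing, or that overfitting will carry it wherever the empty model fails. The figures do not support that. From 34 to 42 successes the empty model fails, and with 11 noise terms at 34 successes an in-sample pass occurs in only about 4% of runs.

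A reader might also take the Fig. 2 caption as a defect, because it makes modelling follow accurate detection, when failures are likely to be few. The caption describes a sequence. If detection fails, the joint claim in the Discussion already fails, so removing the condition would be a preference and not a correction.

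Finally, (iii) never stands alone, and where the empty model passes, hypothesis (i) is exceeded by a wide margin at participant level. That limits the harm to the readiness claim, but it does not make the statement about prediction true.

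**Conclusion.** The concern holds in a limited form. The acceptance rule for (iii) is badly fixed because it is not tied to the observed success proportion: at 43 or more successes it is met with no predictive value, which is about an even chance if the true success rate is 0.85. In addition, it does not require out-of-sample accuracy, and if judged in-sample it is easily met by noise at 40 to 42 successes with 11 or more terms, though rarely near the two-thirds level.

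The size rests on the assumptions listed in the working, and Step 3 also on independent continuous predictors. If the modelled outcome is instead each participant's proportion of tracked images, the rule for scoring 85% of participants would need defining before these figures apply. If the 85% means the share of true successes predicted as successes, the empty model scores 100% at any success rate, and the weakness is greater.

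**What to change.** In the Hypotheses section and the acceptance paragraph of the Discussion:

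- State that (iii) is judged on cross-validated or optimism-corrected performance, with any variable selection repeated inside each resample.
- Keep the 85% mark, and also require evidence of predictive value beyond the observed success proportion. Examples are a corrected AUC whose confidence interval excludes 0.5, or a positive corrected Brier skill score.
- State that if failures are too few to assess prediction, for example if all 50 succeed, (iii) is reported as not assessable, neither accepted nor failed.

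The added requirement should not be that accuracy is strictly above the observed success proportion. At 50/50 successes that proportion is 100% and cannot be exceeded, and at 48/50 at least 49 correct would be needed, so better tracking would make the hypothesis harder to accept.

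The cost is a change of wording and a little computing. The reported accuracy is likely to be lower, and with few failures (7 at 43 successes) the interval for discrimination will be wide.
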